## Abstract

**Introduction:**

Sepsis is a result of initial over-activation of the immune system in response to an infection or trauma that results in reduced blood flow and life-threatening end-organ damage, followed by suppression of the immune system that prevents proper clearance of the infection or trauma. Because of this, therapies that not only limit the activation of the immune system early on, but also improve blood flow to crucial organs and reactivate the immune system in late-stage sepsis, may be effective treatments. The tyrosine kinase FES may fulfill this role. FES is present in immune cells and serves to limit immune system activation. We hypothesize that by enhancing FES in early sepsis and inhibiting its effects in late sepsis, the severity and outcome of septic illness can be improved.

**Methods and analysis:**

*In vitro* and *in vivo* modeling will be performed to determine the degree of inflammatory signaling, cytokine production, and neutrophil extracellular trap (NET) formation that occurs in wild-type (WT) and FES knockout (*FES^-/-^
*) mice. Clinically available treatments known to enhance or inhibit FES expression (lorlatinib and decitabine, respectively), will be used to explore the impact of early *vs.* late FES modulation on outcomes in WT mice. Bioinformatic analysis will be performed to examine *FES* expression levels in RNA transcriptomic data from sepsis patient cohorts, and correlate *FES* expression data with clinical outcomes (diagnosis of sepsis, illness severity, hospital length-of-stay).

**Ethics and dissemination:**

Ethics approval pending from the Queen’s University Health Sciences & Affiliated Teaching Hospitals Research Ethics Board. Results will be disseminated through scientific publications and through lay summaries to patients and families.

## Highlights

•This will be the first study to explore the utility of FES modulation in the treatment of sepsis.•This study will illustrate the importance of differential regulation of sepsis at both early and late timepoints.•This study will employ *in vivo, in vitro*, and clinical research methodologies to elucidate the role of FES in sepsis.•There exists the potential for off-target effects of the drugs used in this study that may complicate the interpretation of results or outcomes, as they are not specific enhancers or inhibitors of FES.

## Introduction

Sepsis is the leading cause of death among hospitalized patients in North America, and is present in over 50% of adult hospitalizations resulting in death or discharge to hospice care (1). Globally, sepsis accounts for 19.7% of all deaths (2), and is the most expensive healthcare problem requiring in-hospital treatment (3), costing the healthcare system approximately $1 billion per year in Ontario alone ($670 million for severe cases, $420 million for non-severe cases) (4). Importantly, the consequences of sepsis extend beyond the duration of the patient’s hospitalization, with lasting impairments being increasingly recognized as comprising “post-sepsis syndrome” (5); resulting in additional costs to the healthcare system for auxiliary care after discharge. Targeted treatments for sepsis are therefore urgently needed to simultaneously improve patient outcomes and alleviate the burden of sepsis on global healthcare systems.

Sepsis is characterized by widespread inflammation and life-threatening organ dysfunction, resulting from dysregulation of the patient’s response to infection and coagulation cascades (6, 7). Specifically, sepsis occurs upon disruption of the tightly regulated balance of pro- and anti-inflammatory mediators activated in response to pathogen- (e.g., virus, bacteria) or damage-associated molecular patterns (e.g., trauma; PAMPs and DAMPs, respectively) (8). Binding of PAMPs and DAMPs to toll-like receptors (TLRs) on the surface of antigen presenting cells (APCs) and monocytes causes nuclear translocation of nuclear factor kappa light chain enhancer of activated B cells (NF-κB), resulting in expression of genes encoding pro-inflammatory cytokines, tumor necrosis factor (TNF)-α, interferons, and components of complement and coagulation pathways (2). Clinically, activation of these pathways results in hypercoagulation, endothelial dysfunction, and ultimately to end organ damage (2).

While sepsis pathophysiology remains to be fully elucidated, we have previously shown that the FES kinase, which is highly expressed in APCs, plays a role in limiting over-stimulation of the innate immune system (9). *FES* knockout mice are hypersensitive to endotoxin lipopolysaccharide (LPS), a TLR-4 agonist, as a result of overactive TLR-4 signaling-induced innate immune responses (10) including increased transcription of genes encoding pro-inflammatory mediators, such as TNF-α (9). Our group and others have implicated FES as a regulator of TLR-4 signaling (9, 11). TLR-4 is also a critical inducer of both platelet-dependent and -independent NET formation, where neutrophils and platelets express both FES and TLR-4. Hyperactive TLR-4 signaling may therefore exacerbate the immune response and coagulation in severe sepsis (12, 13). Furthermore, *FES* knockout (*FES^-/-^
*) mice demonstrate dysregulation of signal transducer and activator of transcription 3 (STAT3) (13), which plays a vital role in the pathophysiology of sepsis by initiating endothelial dysfunction, vasoplegia, coagulopathy, and multi-organ failure (14, 15). FES may also contribute to thrombin formation (16), which is known to contribute to hypercoagulation during the early inflammatory stage of sepsis (17).

There are currently no approved targeted molecular therapies available for the treatment of sepsis (6). The mainstay of treatment for sepsis involves management of infection, optimizing the patient’s fluid balance, improving hemodynamic stability, and sedative management; however, there is controversy over whether these interventions contribute to reduced mortality and morbidity in this cohort (3, 6, 18). Furthermore, early pre-clinical trials employing anti-TNF antibodies or corticosteroids to block proinflammatory cytokine cascades have since been shown to be ineffective in larger and later-stage clinical trials (3, 6). Identifying and targeting the key events and their regulators that precede these dysregulated immune responses characteristic of sepsis is therefore critical to optimize patients’ responses to systemic infection (6).

Due to its expression in innate immune cells and its involvement in regulating TLR-4 signaling (9, 11), we expect that increased FES expression will limit hyper-inflammatory phenotypes of immune cells (9, 11), reduce platelet aggregation (19), and we hypothesize it will also reduce NET formation (12, 20, 21). Consequently, targeting FES may allow for specific inhibition of two key aspects underlying the pathophysiology of sepsis: the coagulation cascade and the innate immune system. This study aims to elucidate the role of FES in sepsis pathophysiology using both an established mouse model of sepsis and a repository of data from patients with sepsis, as a first step toward being able to develop targeted immune-based therapies to enhance patient care and improve outcomes.

## Overarching hypothesis

We hypothesize that FES expression is related to outcomes in *in vivo* and *in vitro* models of sepsis, as well as in clinical populations of patients with sepsis. We further hypothesize that modulating FES can be used as a method of improving sepsis outcomes. **Figure 1** illustrates the hypothesized role of FES in the pathophysiology of sepsis. **Figure 2** illustrates how FES regulation could be used therapeutically to treat sepsis.

**Figure 1 f1:**
[figure not shown]
Decreased FES levels may correlate with worse septic outcomes by modulating host immune and coagulation pathways. **(A)** FES has been shown to play a role in limiting coagulation cascades through modulation of platelets and we hypothesize a role for FES in decreasing NETosis from neutrophils. Therefore, low FES expression is hypothesized to correlate with reduced lysis of blood clots, and an increase in NETosis in both a platelet-dependent and –independent manner, thus leading to reduced mean arterial pressure (MAP), leading to end organ damage. However, in patients with high FES expression, there is hypothesized to be reduced NETosis, and increased disaggregation of platelets, leading to a less dramatic impact on MAP, and improved perfusion of end organs. **(B)** FES has been shown to suppress the toll-like receptor (TLR) 4 signaling cascade, which leads to the production of pro-inflammatory cytokines regulated by NF-κB and IRF3. In patients with low FES expression, it is hypothesized that this signaling cascade will be poorly regulated, leading to the over-activation of the TLR4 cascade, stimulated by components of bacterial cell walls (lipopolysaccharide) or in response to tissue damage (high mobility group box 1), and ultimately leading to the over-production of inflammatory cytokines. This production of excess cytokines can lead to vasodilation, leading to reduced MAP, and reducing perfusion to end organs. However, with high FES expression, this cascade is tightly regulated, and the over-production of pro-inflammatory cytokines is limited, reducing changes in vasodilation, and preventing drastic changes in MAP, thus protecting end organs. Created with BioRender.com.

**Figure 2 f2:**
[figure not shown]
Therapeutic efficacy of FES expression level changes is stage-dependent. Sepsis can be separated into two stages: early stage, characterized by overactive immune responses leading to decreased end organ perfusion; and late stage, characterized by immune suppression, preventing the efficient clearance of the sepsis-inciting event. **(A)** Due to the over-stimulation of the immune system in early sepsis, treatment with decitabine, known to induce increased *FES* expression, will prevent overactivation of the immune system. **(B)** In contrast, overcoming the characteristic late-stage immunosuppression by treatment with lorlatinib, an inhibitor of FES activity, will promote greater pro-inflammatory cytokine production from immune cells. This increase in immune activation will aid in resolving the inciting event of sepsis. Created with BioRender.com.

## Aims and specific hypotheses

### Cell types responsible for sepsis severity and their effect on sepsis outcomes

This study aims to determine the cell types responsible for increased sepsis severity and their effects on outcomes in WT or *FES^-/-^
* mice. We hypothesize that FES limits over-activation of innate immune cells and suppresses vascular hypercoagulation. We expect that *FES^-/-^
* immune cells will take on a hyper-inflammatory phenotype when stimulated with infectious or damaging agents and will produce increased levels of pro-inflammatory cytokines (such as Interleukin (IL) -1, IL-6, Tumor Necrosis Factor (TNF)-α) and NETs relative to WT mice. *In vivo*, we expect to find an increase in both immune cell numbers and their degree of activation, as well as increased coagulation and end-organ damage in septic *FES^-/-^
* mice compared to WT.

### Timing of FES regulation on sepsis outcomes

This study will aim to evaluate whether FES regulation, and the timing of FES regulation, can affect sepsis outcomes. Early sepsis pathogenesis is characterized by hyperinflammation and coagulation, while late sepsis pathogenesis is characterized by immune suppression and organ dysfunction. It is hypothesized that the observed late-stage immunosuppression is as a commensal response to the initial overactive immune response. The early hyper-inflammatory stage of sepsis is characterized by increased immune cell activation and production proinflammatory cytokine secretion such as IL-1, IL-6, and TNF-α (22), a dangerous condition known as cytokine storm (23). This late stage is characterized by production of anti-inflammatory cytokines, such as IL-10 and Transforming Growth Factor-β (TGF-β), which serve to repress the overstimulated immune cells, reduced antigen presenting cells functions, lymphocyte anergy and apoptosis, and reduced responsiveness to activating stimuli, such as LPS (24). Simultaneous inflammation and immunosuppression is now being described in late-stage sepsis (22), suggesting that while there may be immunostimulatory molecules circulating, immune cells may be unable to appropriately respond to these stimuli. This provides additional rational for regulating FES, as it plays a role in limiting innate immune cell activation in response to stimulatory molecules such as LPS. We therefore hypothesize that artificially enhancing FES activation will improve early-stage sepsis, and that inhibiting FES will improve outcomes in late-stage sepsis. **Figure 2** illustrates the timeline of sepsis and the expected impact of FES regulation at each stage of illness.

### Association between FES expression and clinical sepsis presentation and outcomes

This study will seek to determine whether the RNA expression levels of FES are associated with the incidence, severity, and outcome of sepsis using bioinformatic analysis. We expect that FES will be upregulated in early-stage and downregulated in late-stage sepsis. Furthermore, we hypothesize that decreased *FES* RNA levels will be associated with receiving a clinical diagnosis of sepsis, increased illness severity, and poorer clinical outcomes including greater risk for ICU mortality and increased length of hospitalization.

Furthermore, we aim to determine whether clinical sepsis outcomes are correlated with single nucleotide polymorphisms (SNPs) associated with differential *FES* expression. Recently, two SNPs have been associated with reduced *FES* expression: rs17514846, located within in the 5’ proximal region of the neighbouring gene *FURIN*, and rs1894401, located within the *FES* gene. The presence or absence of these two SNPs will be correlated with clinical outcomes in a cohort of sepsis patients (25).

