### Clinical and bioinformatics methodology

We have previously extracted RNA from whole blood samples in critically ill patients at various time points during their admission, as well as from healthy controls, as part of the “Prevention of nosocomial infections in critically ill patients with lactoferrin (PREVAIL)” study (NCT01996579). Briefly, blood was collected into PAXgene tubes, frozen, RNA extracted, and gene expression was profiled using the Affymetrix PrimeView microarray (40). Data on 69 patients and 21 healthy controls from this analysis is publicly available (41) and will be analyzed for the current study. Machine-learning approaches will be used to identify key variables associated with FES RNA expression levels, including a) *clinical diagnosis of sepsis*; b) *illness severity*, as measured by Acute Physiology and Chronic Health Evaluation II (APACHE II) and Sequential Organ Failure Assessment (SOFA) scores; and c) clinical outcomes including *hospital length of stay and ICU mortality*.

A publicly available dataset comprised of clinical outcome data as well as SNP analysis from genome wide association studies (GWAS) will be sought through collaborations with local and international experts in the field of sepsis genetics. Multivariable analysis will be used to determine the association between the two SNPs (rs17514846 and rs1894401) related to differential FES expression, and clinical, patient-centred outcomes. Additionally, we will apply for access to the United Kingdom BioBank (https://www.ukbiobank.ac.uk/), a large-scale database with in-depth genetic and clinical outcomes for a wide variety of diseases (including sepsis) in over half a million patients. This database currently has SNP and transcriptomic data available to be paired with clinical outcomes and will soon be releasing proteomic data which can be analyzed further to pair the two SNPs (rs17514846 and rs1894401) related to differential FES expression with protein expression, and clinical outcomes.

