While it is our expectation that high FES expression levels in early sepsis and low FES expression levels in late sepsis will result in improved murine and patient outcomes, it is possible that this will not be the case. However, irrespective of the direction of the association, we will capitalize on the FES expression results found in order to improve *in vitro*, *in vivo* outcomes. For example, if we find that low FES expression is associated with improved outcomes in early sepsis (contrary to our hypothesis), we will expand upon this finding by seeking to reduce FES expression in our models of early sepsis. Similarly, if–contrary to our expectations–we find that high FES expression is associated with improved outcomes in late sepsis, we will aim to increase FES expression in our models of late sepsis and evaluate changes in outcomes seen as a result of this shift in expression. Additionally, if FES expression plays no role in sepsis severity, it will allow us to rule out a potential regulator heavily involved in many aspects of sepsis, which will help to narrow in on true regulators of sepsis severity and outcomes. We expect that *FES* expression levels on microarray analysis can be used alone or in combination with other genetic features as a biomarker to determine the presence, stage, severity, and outcome of sepsis. The heterogeneity of sepsis presentation and progression has long posed a problem for determining which patients will benefit from specific therapies, and the appropriate timing of these interventions. If we find that FES expression differs between time points in the progression of septic illness (i.e., between early- *vs*. late-stage sepsis), these results may then be used in future studies to help with targeting treatments toward specific subsets of patients who may differentially benefit from therapeutic interventions applied at different time points.

Finally, we expect that two SNPs associated with differential FES expression will be useful as prognostic biomarkers to stratify patients with sepsis based on risk for adverse outcomes that are relevant to patients, with the potential predictive value to inform FES-targeted treatments based on risk.

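### The clinical hypothesis on FES RNA has no stage qualifier and conflicts with the article's own stage-specific expectations, for outcome in late samples and for diagnosis in early ones

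*Protocol article*

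**What the plan says.** Under *Association between FES expression and clinical sepsis presentation and outcomes*, the protocol article makes two predictions in consecutive sentences. The first is about level by stage: "We expect that FES will be upregulated in early-stage and downregulated in late-stage sepsis". The second is about association, with no stage attached: "decreased *FES* RNA levels will be associated with receiving a clinical diagnosis of sepsis, increased illness severity, and poorer clinical outcomes". The outcomes named there include ICU mortality and length of hospitalisation. The legend to Figure 1 gives the same unstaged direction.

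Under *Expected impact*, the authors state their expectation that "high FES expression levels in early sepsis and low FES expression levels in late sepsis will result in improved murine and patient outcomes". Under *Timing of FES regulation on sepsis outcomes*, the matching hypothesis for intervention is that "artificially enhancing FES activation will improve early-stage sepsis, and that inhibiting FES will improve outcomes in late-stage sepsis".

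The data are described under *Clinical and bioinformatics methodology*. RNA came from "whole blood samples in critically ill patients at various time points during their admission", and on size the article says: "Data on 69 patients and 21 healthy controls from this analysis is publicly available". The analysis is given as: "Machine-learning approaches will be used to identify key variables associated with FES RNA expression levels". The variables then listed are diagnosis of sepsis, APACHE II and SOFA scores, hospital length of stay and ICU mortality. Neither stage nor sampling time is named.

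**The concern.** The expected direction of the FES-outcome association is the core of the clinical aim, and the article gives two directions for late sepsis. Since the dataset already exists and is public, a direction fixed in advance is one of the few safeguards available. With both signs on record for late samples, either late-stage result agrees with one of the two statements.

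The direction also has consequences. *Expected impact* sets out what follows if the expectation fails: if low FES goes with better outcomes early, the team will try to lower FES in its early-sepsis models, and if high FES goes with better outcomes late, it will try to raise FES in its late-sepsis models. Those rules need a separate answer for each stage. A single association over samples from mixed times cannot supply one.

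**Working it through.** **Step 1. Set the predictions side by side.**

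| Comparison | Source | Early samples | Late samples |
|---|---|---|---|
| Sepsis versus no sepsis | Association hypothesis (no stage) | FES lower in sepsis | FES lower in sepsis |
| Sepsis versus no sepsis | Level-by-stage sentence, same section | FES higher | FES lower |
| Outcome among patients | Association hypothesis (no stage) | low FES, worse | low FES, worse |
| Outcome among patients | *Expected impact* | high FES, better | low FES, better |

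The unqualified hypothesis is read here as applying to both columns. The statements conflict in two cells: diagnosis in early samples and outcome in late samples. They agree in the other two.

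The late-outcome conflict cannot be explained as association versus drug effect, because *Expected impact* also speaks of expression levels and patient outcomes. An early-only reading of the association hypothesis is hard to sustain, because the sentence before it names both stages.

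**Step 2. What pooling would do if the stage hypothesis is true.** The article gives no effect size, significance level, power or stage split for this aim, so there is no figure to reproduce. What follows is an illustration.

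Input from the article: 69 patients.

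Assumptions:
- FES correlates with good outcome at +r in early samples and -r in late samples.
- Means and variances are equal across stages.
- Each patient contributes one sample, and all 69 can be staged.
- The test is two-sided at 5%.

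With p the share of late samples, the pooled correlation is r(1 - p) - rp = r(1 - 2p). Power from Fisher's z, with m = atanh(pooled r) × √(69 - 3), is Φ(m - 1.96) + Φ(-m - 1.96).

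For r = 0.4:

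| Late share | Pooled r | Power |
|---|---|---|
| 0% | 0.40 | 93% |
| 10% | 0.32 | 77% |
| 25% | 0.20 | 38% |
| 33% | 0.14 | 20% |
| 50% | 0.00 | 5% |
| 75% | -0.20 (reversed) | 38% |

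Worked line for 25% late: 0.4 × (1 - 0.5) = 0.20; atanh(0.20) = 0.2027; m = 0.2027 × 8.124 = 1.647; Φ(-0.313) = 0.377.

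Range over r at 25% late: r = 0.3 gives a pooled 0.15 and 23% power; r = 0.5 gives 0.25 and 55%.

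**Step 3. Relax the equal-and-opposite assumption.** With +0.4 early, -0.2 late and half the samples late, the pooled value is 0.5 × 0.4 - 0.5 × 0.2 = 0.10, with 13% power.

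**Step 4. Let the stages differ in mean.** Keep r = 0.4, equal and opposite, with half the samples late. Suppose FES differs by 1 SD between stages and outcome by 0.5 SD. The within-stage part is then zero, and stage alone gives 0.25 × 1 × 0.5 / √(1.25 × 1.0625) = 0.11 in absolute value. So a pooled result can also be confounded by stage.

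**The case against.** The strongest reply is that the article commits to no stage-free analysis. Its list of variables is introduced as an open one, machine-learning methods can carry interactions, and model terms are what a condensed article leaves to the full protocol or analysis plan. *Expected impact* also treats stage as something FES might identify, and discusses whether FES differs between early and late time points. This stands. A reader might infer that the plan will pool over stages; the text does not establish that. The early-late comparison it mentions, however, concerns the level of FES, not its association with outcome by stage, and no model term would reconcile the two written hypotheses.

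A reader might also infer that the article claims low FES is harmful at every stage, or that pooling must cancel the effect. The hypothesis simply names no stage. Exact cancellation with equal and opposite effects needs a half-and-half mix, and the article gives neither effects nor mix.

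Third, a reader might take a stage comparison in all 69 patients to be well powered: at r = 0.4 and a 35/34 split, 2 × 0.4236 / √(1/32 + 1/31) = 3.36, or about 92%. The article does not support that. The patients are described as critically ill, with sepsis diagnosis a variable to be examined, so the number with sepsis is unknown. If it were 35 (assumed), split 18/17, the same formula gives 0.847 / √(1/15 + 1/14) = 2.28, or about 63%. Sampling at various times may also mean repeated, correlated samples per patient.

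Fourth, the therapeutic rationale is tested mainly in mice, with drug given at 1h or 12h; the clinical aim is exploratory. That stands, and it lowers the severity. It would be too strong to say that the clinical aim can refute nothing: a pooled association of high FES with worse outcome would contradict the unqualified hypothesis.

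**Conclusion.** The point holds as a contradiction in the stated hypotheses. For outcome in late samples, and for diagnosis in early samples, the article predicts both signs. That conclusion rests on the text alone.

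The consequence for analysis is conditional. If the article's stage hypothesis is true and samples are pooled over stages, the association is attenuated, cancelled, reversed or confounded by stage, depending on the mix, and it cannot feed the stage-specific follow-on rules. The correlations, significance level and stage shares used to show its size are assumptions. So are one sample per patient and a sepsis stage for all 69.

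Severity is moderate: worth correcting before FES is analysed, but not critical, since this is an exploratory analysis of an existing dataset and a stage term is not excluded.

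**What to change.** 1. Reconcile the association hypothesis with *Expected impact* by restating it separately for early and late sepsis. Do the same for diagnosis, giving the expected direction against the comparison group at each stage.
2. Define early and late by sampling time before FES is examined, as far as the dataset records it. The article does not say whether sepsis onset is available. Time from ICU admission need not equal sepsis stage, so the choice should be stated with that limit.
3. Among patients with sepsis, estimate the FES-outcome association within each stage or with a FES-by-stage interaction, allowing for any repeated samples from the same patient. Report the number of septic patients and samples per stage.

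The cost is a change of wording and, where timing is recorded, one further term in the model. The downside is precision: stage-specific estimates are less precise than a pooled one, and power depends on a number of septic patients that the article does not give, so no power should be claimed until that number is known.

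### The only SNP coding stated is binary, which discards allele dose, and no described step tells a FES effect from one through neighbouring FURIN

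*Protocol article*

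**What the plan says.** The aims subsection on FES expression and clinical sepsis introduces the two variants and where they lie:

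- "two SNPs have been associated with reduced *FES* expression: rs17514846, located within in the 5’ proximal region of the neighbouring gene *FURIN"
- The second variant, rs1894401, is placed inside FES itself.

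It then says how they will be used: "The presence or absence of these two SNPs will be correlated with clinical outcomes in a cohort of sepsis patients".

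The section on clinical and bioinformatics methodology adds: "Multivariable analysis will be used to determine the association between the two SNPs (rs17514846 and rs1894401) related to differential FES expression". It names no genetic model, effect allele or covariates. It also says that UK Biobank holds SNP and transcriptomic data, and that proteomic data, once released, could be used to pair the two SNPs "related to differential FES expression with protein expression, and clinical outcomes".

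The section on expected impact gives the intended reading. First, "we expect that two SNPs associated with differential FES expression will be useful as prognostic biomarkers". Then comes a further step, "with the potential predictive value to inform FES-targeted treatments based on risk".

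FURIN is named once, to locate rs17514846. The article does not mention FURIN expression, correlation between the two SNPs, conditional analysis or colocalisation.

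**The concern.** There are two separate issues, and solving one does not solve the other.

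**Coding.** The SNPs were chosen because they are linked to lower FES expression, which is a quantity. The expected-impact section itself argues that the amount of expression matters. A yes/no variable puts a person with one copy and a person with two copies in the same group. It also leaves open which allele counts as present. If each copy shifts the outcome, the analysis gives up information that the genotype already holds.

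**Attribution.** A prognostic marker needs no known causal gene. A genotype meant to inform FES-targeted treatment does, because the claim depends on the effect running through FES. By the article's own description one of the two variants lies beside another gene. If an association at rs17514846 did run through FURIN, nothing in the described analysis would show it, and the result would count as support for FES.

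**Working it through.** The article gives no sample size, power, effect size or allele frequency for the SNP analysis, so there is no stated figure to reproduce. The size of the coding loss can be shown over a range.

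**Assumptions (none from the article).** Hardy-Weinberg proportions; a purely per-allele effect; allele frequency p for the allele counted as present, with q = 1 − p; and, for the power column, 80% power for 0/1/2 coding at two-sided 0.05.

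**Efficiency.** Let G be the allele count and C the carrier indicator (G of 1 or 2). The efficiency of C relative to G is their squared correlation.

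- Var(G) = 2pq
- P(C = 1) = 1 − q², so Var(C) = q²(1 − q²)
- Cov(G, C) = 2p − 2p(1 − q²) = 2pq²
- r² = (2pq²)² / [2pq · q²(1 − q²)] = 2pq / (1 − q²) = 2q / (1 + q)

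The sample-size multiplier is 1/r². Power is Φ[(1.960 + 0.842)·√r² − 1.960]. The share of carriers with two copies is p² / (1 − q²).

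| p | r² | Information lost | N multiplier | Power with carrier coding | Carriers with two copies |
|---|---|---|---|---|---|
| 0.05 | 0.974 | 2.6% | 1.03 | 79.0% | 2.6% |
| 0.10 | 0.947 | 5.3% | 1.06 | 77.8% | 5.3% |
| 0.20 | 0.889 | 11.1% | 1.12 | 75.2% | 11.1% |
| 0.30 | 0.824 | 17.6% | 1.21 | 72.0% | 17.6% |
| 0.40 | 0.750 | 25.0% | 1.33 | 67.9% | 25.0% |
| 0.50 | 0.667 | 33.3% | 1.50 | 62.8% | 33.3% |

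Worked line: at p = 0.5, r² = 2(0.5)/1.5 = 0.667 and 1/0.667 = 1.50.

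**Two properties of this result.**

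- The squared correlation is symmetric. If the true effect were strictly dominant, 0/1/2 coding would lose the same fraction relative to carrier coding.
- The table takes the counted allele to be no more common than the other. Counting an allele with frequency 0.9 gives r² = 2(0.1)/1.1 = 0.182. With 0/1/2 coding, swapping the allele changes only the sign of the estimate. This is a practical reason to name the effect allele.

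**Attribution.** No arithmetic applies, so the statements are set side by side.

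- Location: one SNP lies near FURIN, the other within FES.
- Basis for selection: both are linked to reduced FES expression. Nothing is said about FURIN expression.
- Analysis: both are tested against outcomes, and pairing with protein expression is planned without FURIN being named.
- Inference: prognosis, which needs no causal gene, and possible use for FES-targeted treatment, which does.

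The last inference needs a step that the analysis, as described, does not contain.

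**The case against.** The strongest reply is that the binary phrase is general wording in the aims. The methods section fixes no coding, and genetic models, effect alleles and ancestry covariates are normally settled in an analysis plan. That stands in part: binary coding should not be read as a settled specification. It is nevertheless the only coding the article states, and the methods do not replace it.

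Second, the size of the loss is conditional. The article does not say that the effect is per allele. The loss is only 3% to 5% for frequencies of 0.05 to 0.10, and one third is the top of the tabulated range. UK Biobank is also large, "in over half a million patients", although the number with sepsis is not given. All of this stands.

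A reader might infer more than the document supports:

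- **That the study cannot separate FES from FURIN.** This ignores the within-FES SNP and the transcriptomic and protein data, which could address the question if FURIN were examined too.
- **That rs17514846 acts through FURIN, or that the two SNPs are correlated and would split one signal in a joint model.** Neither the effect nor the correlation is in the article, and it does not say that both SNPs enter one model.
- **That every SNP result is read as a FES effect.** Most of the text speaks of correlation, association and prognosis. Only the treatment clause goes further, and it is hedged.
- **That binary coding has no benefit.** It is the more powerful choice if the effect is strictly dominant.

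**Conclusion.** The point holds in two limited parts.

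On coding, the wording taken literally pools one-copy and two-copy carriers. Under Hardy-Weinberg proportions and a per-allele effect, it loses about 5% of the information at a frequency of 0.1 and 33% at 0.5, equivalent to needing 1.06 to 1.50 times the sample. Where the two SNPs fall in that range cannot be read from the article.

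On attribution, no described step distinguishes a FES effect from a FURIN effect, so a SNP association alone would not support the clause on FES-targeted treatment. This is a gap in the described inference. It is not evidence that FURIN is responsible, and the prognostic use of the SNPs is unaffected.

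**What to change.** 1. Name the effect allele for each SNP. Make 0/1/2 coding the primary analysis and carrier coding a sensitivity analysis.
2. Report each SNP singly, then both jointly, with the correlation between them.
3. Use the transcriptomic and protein data already in view to examine FES and FURIN expression together, for example by conditional or colocalisation analysis.
4. Unless that evidence points to FES, report a FURIN-FES locus association, and not a FES effect or a basis for FES-targeted treatment. An association at rs1894401 alone should not count as proof of a FES mechanism: lying within a gene does not show action through it, and if the SNPs are correlated the signal could reflect the other variant.

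Items 1, 2 and 4 cost only wording and a few extra model fits. The genetic dataset is still being sought and UK Biobank access is still to be requested, so they can be fixed before any result is seen. Item 3 adds some analysis and depends on FURIN being measured in those data, which the article does not say. The statistical downside is lower power if the effect is strictly dominant, and the carrier sensitivity analysis covers that case.
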